### Inclusion and Exclusion Criteria

Inclusion criteria for participation are shown in Textbox 1. Exclusion criteria for participation are shown in Textbox 2.

Inclusion criteria.Overweight or obese (body mass index between 25 and 55 kg/m^2^)Employed full time at Penn State Hershey Medical Center and physically present in the office a minimum of 35 hours per week to ensure it is feasible to complete daily pedalingWork between 6 am and 6 pm, Monday through Friday, as this is the time frame during which study staff are available to oversee the programDesk-based office job involving sedentary work for ≥5 hours per day, 5 days per week
Use a nonshared desk so the pedaling measured can be attributed to the study participantAged between 18 and 70 yearsAble to read and speak EnglishOwn an Android or iPhone smartphone with internet or Wi-Fi access and willing to install the free Cubii cycling app (Fitness Cubed Inc) needed for all study conditions on their smartphone
Work in a campus building that has at least one onsite Hershey-operated food vendor. On the basis of research showing the importance of resource proximity for resource use [45,46], the food-based rewards are more likely to be used if they are easily accessibleAble to obtain their supervisor’s approval to participateAble to identify a coworker to do the program together with, who also meets all eligibility criteria after separately completing the screening form, based on evidence that social environment support can promote physical activity [45,47,48]

Exclusion criteria.Currently pregnantHealth or personal condition (eg, planned surgery) that could prevent program completionPhysical Activity Readiness Questionnaire [49] response indicating that participants (1) have been advised that they have a heart condition and should only do physical activity recommended by their doctor or (2) have chest pain during physical activityPlanned travel or relocation that will lead participants to be unavailable for 3 or more days during the study and that cannot be accommodated by adjusting the program datesAlready have a cycling device or treadmill workstation at their desk

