### Intervention Procedures

#### Common Elements

Participants in all 6 conditions are provided with the Cubii Pro elliptical (Fitness Cubed Inc) at no cost (Figure 1). During an approximately 1-hour elliptical setup meeting, research staff work with each participant to set up the desk elliptical ergonomically, including placing the elliptical at a comfortable distance and angle from the participant’s chair and keyboard and equipping participants with rubber mats and chair anchors to prevent excess chair and elliptical motion while pedaling.

During the elliptical setup meeting, research staff also install the free Cubii elliptical app on each participant’s Android or iPhone smartphone. This app provides participants with real-time automated feedback on both their own and their partner’s pedaling volume (ie, miles, strides, minutes, and calories expended), and shows a bicyclist moving in real time in sync with each participant’s pedaling (Figure 2). Research staff demonstrate key app features to participants and explain how to check the elliptical is connected to the app to prevent loss of pedaling data. Research staff also link each participant’s pedaling data to a research-administered Cubii server account and Fitbit account to enable automatic uploading of each participant’s pedaling data. Although the Cubii server data can only be obtained by the researchers on a delayed basis, participants’ pedaling data on the Fitbit site are available continuously—enabling research staff to monitor pedaling adherence in real time.

All participants are asked to attempt to pedal the elliptical at least 2 miles daily (approximately 1 hour of daily pedaling) from Monday through Friday. The goal of 2 miles, or 1 hour, of daily pedaling was determined by prior studies, which suggested that this goal could have a clinically significant impact on weight gain prevention while being feasible for overweight and unfit participants [11,13]. Participants are informed that they can choose to pedal more or less than the 2-mile goal and are advised to self-select a comfortable pedaling pace, intensity, and duration. Participants are also advised that they can pedal the desk elliptical in short bouts of a few minutes at a time or in longer bouts. Although participants are asked to attempt to pedal on all 5 workdays, they are informed that it is understandable if they occasionally need to miss a day or reduce their pedaling.

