**Employee ratings of work performance**				
	1. The World Health Organization Health and Work Performance Questionnaire: Employees rate overall work performance in previous 4 weeks on a 10-point scale; lower employee-rated work performance associated with odds of lower performance in supervisor evaluations and records and experience sampling across multiple job types (odds ratios: 3.2-12.3, *P* values<.05) [55].	X^d^	—^e^	X
	2. Employees rate work quantity, work quality, and interaction quality in previous 4 weeks on a 5-point scale; evidence of face validity [56]; higher work quantity associated with higher physical fitness (*P*=.045), higher work quality associated with higher moderate physical activity (*P*=.002), lower interaction quality associated with greater obesity (*P*=.02) [57].	X	—	X
	3. Work performance by task type: Employees rate ability to perform common work tasks (eg, emails and phone calls) during elliptical use in previous 4 weeks, using a 5-point investigator-generated scale.	—	—	X

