#### Effects of Desk Pedaling on Work Performance

For the study’s first goal, to test whether mean work performance scores during the 4-week desk pedaling intervention period are equivalent to performance during the 4-week preintervention period with standard office sitting, we will apply the equivalence test of means based on 2 one-sided *t* tests [64,65] with the significance level adjusted for multiple comparisons via the Bonferroni correction factor. We will also use the confidence interval approach for testing equivalence when regression models are considered [66].

We define equivalence based on 2 related standards: (1) the International Organization of Standardization ergonomic standard for computer keyboards indicates that average typing speeds obtained using a new keyboard must not exceed 0.75 standard deviations of average speeds for standard keyboards (in the direction of poorer performance) to be acceptable [67]; (2) in clinical research, a change of 0.50 standard deviations in health status sometimes is used as a basis for treatment modifications [68,69]. Using the approximate midpoint of these 2 standards, we define equivalence, or feasibility, for the desk elliptical as average work performance scores that do not exceed 0.60 standard deviations (in the direction of poorer performance) of average work performance scores obtained during standard office sitting.

We will also explore how work performance varies by tertiles of elliptical pedaling quantity. To evaluate changes in overall work performance, and work performance by task type, which are repeatedly measured, we will plot mean scores over time and conduct longitudinal analysis based on mixed effects models [70]. We will use random effects to account for measurement correlation within the same subject and clustering effects. The estimated time effect from mixed effects models will indicate whether performance increased, decreased, or remained stable over the preintervention and intervention periods.

For the qualitative assessment of participants’ capacity to pedal and work simultaneously, NVivo software (QSR International) will be used to organize data from the qualitative open-ended questions. A codebook will be developed to classify major themes, and data will be coded by 2 independent coders. Coding discrepancies will be discussed and resolved, and interrater reliability will be calculated.

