#### Power and Sample Size

We assume that an equivalence margin standardized by the standard deviation is 0.60 for the primary outcome, based on clinical and industrial engineering standards [67-69]. We also assume an intracluster correlation of 0.05 and a significance level of 0.05. Therefore, a sample size of 50 (25 dyads) gives 80% power to detect equivalence when assessing the mean delta change in total work performance scores from the preintervention period to the intervention period. Anticipating 10% to 20% attrition, we expect to recruit up to 60 participants. The study was not powered to detect differences in pedaling volume by the 6 incentive conditions because of resource constraints and because a key exploratory goal was to assess feasibility and preliminary effects of different incentive strategies.

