### Conclusions

Demonstrating that people can simultaneously pedal compact devices and work productively, and that they are willing to sustain this pedaling, will set the stage for future trials to (1) track longer term effects of desk pedaling on health outcomes and work performance in diverse populations and (2) evaluate effects of automated real-time feedback and incentive systems to sustain desk pedaling. Ultimately, these initiatives will grow the evidence base needed to build workplaces that support active lifestyles as a normative occupational practice.

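### The 0.60 SD equivalence test on 4-week whole-job ratings fits the stated hypothesis but cannot by itself show that people work productively while pedaling

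*Protocol article*

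**What the plan says.** **Criterion.** The protocol article, Effects of Desk Pedaling on Work Performance, states: "we define equivalence, or feasibility, for the desk elliptical as average work performance scores that do not exceed 0.60 standard deviations". The limit applies to worsening, and the reference is standard office sitting. The test is two one-sided t tests with a Bonferroni correction. Power and Sample Size repeats the margin: "We assume that an equivalence margin standardized by the standard deviation is 0.60 for the primary outcome".

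**Source of the margin.** Two standards are named. One is ergonomic: "average typing speeds obtained using a new keyboard must not exceed 0.75 standard deviations of average speeds for standard keyboards". The other is a 0.50 SD change in health status, used in clinical research as a basis for changing treatment. The figure 0.60 is described as their approximate midpoint.

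**What is rated.** Table 1: "Employees rate overall work performance in previous 4 weeks on a 10-point scale". The work quantity, work quality and interaction quality items cover the same 4 weeks, and supervisors complete adapted versions of both instruments. One further rating concerns time on the device: "Employees rate ability to perform common work tasks (eg, emails and phone calls) during elliptical use". Table 1 schedules it at M2 (postintervention) only.

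**Dose and working time.** Common Elements asks participants to try to pedal "at least 2 miles daily (approximately 1 hour of daily pedaling) from Monday through Friday". Inclusion and Exclusion Criteria require employees to be "physically present in the office a minimum of 35 hours per week" and to have at least 5 hours of sedentary desk work per day.

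**Conclusion sought.** Discussion, Conclusions: "Demonstrating that people can simultaneously pedal compact devices and work productively" is to prepare the way for later trials. The Abstract's Background and Principal Considerations also use feasibility to mean pedaling and office work at the same time.

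**The concern.** The quantity tested and the quantity in the claim differ. The test compares two 4-week periods on ratings of the whole job. The claim is about work done during pedaling. At the goal dose, roughly six of every seven rated office hours involve no pedaling, even if every participant meets the goal every day. A loss confined to pedaling time is therefore averaged with a much larger amount of unaffected work. A margin taken partly from a standard for performance while a device is in use does not keep that meaning on such a rating.

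The article itself says that employers will need evidence on work performance before desk ellipticals spread widely. If a pass is read as proof that people work as well while pedaling as while sitting, employers would be told something the primary test has little ability to contradict.

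**Working it through.** **1. Reproduce the stated power.** Inputs from Power and Sample Size: margin 0.60 SD, intracluster correlation 0.05, significance level 0.05, 50 participants in 25 dyads, 80% power.

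- Design effect = 1 + (2 − 1) × 0.05 = 1.05, so effective n = 50 / 1.05 = 47.6.
- The SD of the change is √(2(1 − r)) × SD, where r is the pre-post correlation. The article does not give r.
- With r = 0: SE = √(2 × 1.05 / 50) = 0.205 SD. With r = 0.5: SE = √(1.05 / 50) = 0.145 SD.
- Normal approximation: P(declare equivalence | true shift δ) = Φ((0.60 − δ)/SE − z) + Φ((0.60 + δ)/SE − z) − 1, with z = 1.645 for alpha 0.05 per one-sided test.
- At δ = 0 this gives 0.80 for r = 0, which reproduces the stated figure, and 0.99 for r = 0.5. The range from r = 0 to r = 0.5 is carried through below.

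**2. Share of rated time spent pedaling.** 35 hours / 5 days = 7 hours per day, so f = 1/7 = 0.143 at full goal adherence. An 8-hour day (assumed) gives 1/8 = 0.125. Counting only the minimum 5 sedentary hours gives 1/5 = 0.20.

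**3. Translate an in-use loss to the whole-job scale.** Assume that the 4-week rating is a linear time average, that nothing spills over into non-pedaling time, and that in-use and whole-job performance share one SD. Then overall loss = f × in-use loss. A loss at the keyboard limit becomes 0.75 / 7 = 0.107 SD. On the 5-hour basis it is 0.75 / 5 = 0.15 SD.

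**4. Probability that the test declares equivalence** (r = 0 to r = 0.5):

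| In-use loss | Overall loss, f = 1/7 | alpha 0.05 | alpha 0.05/4 = 0.0125 |
|---|---|---|---|
| 0 | 0 | 0.80 to 0.99 | 0.51 to 0.94 |
| 0.75 SD | 0.107 SD | 0.74 to 0.96 | 0.45 to 0.87 |
| 1 SD | 0.143 SD | 0.70 to 0.93 | 0.41 to 0.82 |
| 2 SD | 0.286 SD | 0.45 to 0.70 | 0.22 to 0.47 |

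The last column uses z = 2.241. Four comparisons is an assumption, because the article does not state the number.

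Worked line for 0.75 SD, r = 0, alpha 0.05: (0.60 − 0.107)/0.205 − 1.645 = 0.76, Φ = 0.776; (0.60 + 0.107)/0.205 − 1.645 = 1.81, Φ = 0.965; 0.776 + 0.965 − 1 = 0.74.

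**5. Comparisons.** On the 5-hour basis the 0.75 SD loss still passes with probability 0.69 to 0.93 at alpha 0.05. If the same loss fell undiluted on the rated scale, it would pass less than 1% of the time.

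**6. The task-type scale.** The analysis section groups work performance by task type with the repeatedly measured outcomes and plans plots over time and mixed models. Table 1 gives that scale one time point, M2. A time effect cannot be estimated from one measurement per participant.

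**The case against.** The strongest reply is that the test matches the hypothesis the article declares. Purpose and Hypotheses compares a 4-week pedaling period with a 4-week sitting period, and Design and Power and Sample Size use the same contrast. For an employer, whole-job performance under the programme is a sensible target, and about 1 hour a day is the intervention itself. This stands: the test is not the wrong test for its hypothesis, and nothing here calls for replacing it.

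Several stronger readings are tempting, and the documents do not support them:

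- *The margin comes wholly from standards for performance during device use.* Only the keyboard standard does. The 0.50 SD source concerns health status.
- *Nothing in the plan addresses work during pedaling.* The task-type ratings, the analysis by tertiles of pedaling quantity and the coded open-ended responses all bear on it. None of them enters the printed definition of feasibility.
- *The Abstract's Conclusions make the same overreach.* That text asks whether pedaling can be sustained without harming work performance, which is a programme-level statement.
- *The test tolerates an in-use loss of 0.60 × 7 = 4.2 SD.* That is the loss that would sit on the margin under the averaging assumptions (3.0 SD with 5 hours, 4.8 SD with 8). The article gives no SDs or in-use effects, and participants may pedal more than the goal, so it is not a property of the trial.

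It is also fair that the Discussion sentence looks ahead to later trials and is not a decision rule, and that the Bonferroni correction lowers the pass probabilities. With r = 0 and 4 comparisons, however, no loss passes 0.51 of the time and a 0.75 SD in-use loss 0.45, so the test still hardly separates the two.

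**Conclusion.** The point holds as a limit on what may be concluded. Passing the 0.60 SD test supports a statement about overall 4-week work performance under a programme with a goal of about 1 hour of daily pedaling. It does not by itself support reading feasibility as productive work while pedaling, which is how the Abstract's Background, Principal Considerations and the Discussion's Conclusions frame the question, and which the analysis section's definition of feasibility invites.

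The mismatch follows from the printed dose, office hours and recall window, and it remains at full adherence to the goal. Its size is illustrative only: a 0.75 SD in-use loss seen as about 0.11 SD and passed with probability 0.74 to 0.96, or 0.45 to 0.87 with 4 comparisons. Those figures rest on linear time-weighting, no spillover, a common SD and a pre-post correlation between 0 and 0.5. Spillover of any harm into non-pedaling hours would make the test more sensitive. Adherence below the goal would make it less so.

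Separately, and without any such assumption, the longitudinal model planned for the task-type scale cannot be fitted on the schedule in Table 1.

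**What to change.** 1. Keep the equivalence test and its margin. In Effects of Desk Pedaling on Work Performance and in the Discussion's Conclusions, state that passing it shows only that a programme with a goal of about 1 hour of daily pedaling does not lower overall 4-week work performance by more than 0.60 SD.
2. Base statements about working while pedaling on the task-type ratings, reported for each task as a mean with a confidence interval at M2, beside the planned tertile and qualitative analyses.
3. Remove the task-type scale from the longitudinal mixed-model plan and put the summary in item 2 in its place.

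A pass/fail cut-off on the task-type scale is not proposed. Its anchors are not shown and it has no baseline, so any threshold would be a matter of preference.

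Cost: changes of wording and one summary of data already collected, with no new participants or measurements. The downside is a narrower headline claim, and a claim about simultaneous work that depends on an investigator-generated scale without a sitting comparison.

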### Desk Pedaling and Work Performance

To disseminate desk ellipticals or similar devices on a large scale, employers will require evidence that pedaling such devices does not compromise work performance [19,20]. Most previous studies that assessed simultaneous work performance during desk pedaling were conducted in lab-based settings [21-26]. These lab-based studies supported the feasibility of completing specific work tasks during simultaneous desk pedaling, within controlled environments that maximized internal validity [27]. However, there has been limited research on work performance and simultaneous desk pedaling in field settings where employees perform their actual jobs. Conducting work performance evaluations in field settings is important for the external validity of study findings, as these settings may include unique social and built environment constraints or facilitators (eg, coworker criticism or praise, and office layout variations) that are difficult to engineer in a lab [27,28].

Among several studies that investigated the use of compact elliptical or pedaling devices in real-world offices, employee-administered surveys suggested that it was feasible to work productively while engaged in simultaneous pedaling [13,29,30]. However, these studies lacked input from supervisors about the effects of pedaling devices on employee performance—which is needed to ensure more widespread acceptance and dissemination of these devices. These studies also lacked assessment of employees’ ability to perform specific common office work tasks (eg, emails and phone calls) while pedaling. Therefore, a more comprehensive assessment of work performance during office-based pedaling is warranted.

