### Purpose and Hypotheses

In sum, we aim to present the rationale and methods for a randomized trial among overweight and obese employees that will assess the effects of (1) desk pedaling on work performance using comprehensive employee- and supervisor-rated work performance measures and (2) healthier food versus monetary incentives with varied reinforcement schedules on pedaling quantity. We hypothesize that a 4-week desk pedaling intervention period, as compared with a 4-week preintervention period of standard office sitting, will not yield meaningful differences in employees’ work performance. We also hypothesize that healthier food and monetary incentives delivered (1) on an immediate rather than a delayed schedule, and (2) partially contingent on dyadic- rather than solely individual-goal achievements, will yield greater pedaling quantity. Achieving these aims could help bridge the research-to-practice gap in translating desk ellipticals from laboratory settings to real-world office environments.

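### The feasibility criterion bounds only a decline in work performance, but the named test (TOST) also needs an upper margin that is never stated

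*Protocol article*

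**What the plan says.** All references are to the protocol article.

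- **Test.** Effects of Desk Pedaling on Work Performance: "we will apply the equivalence test of means based on 2 one-sided" t tests, with the "significance level adjusted for multiple comparisons via the Bonferroni correction factor". The number of comparisons is not given.
- **Success criterion.** The next paragraph of that section defines equivalence, or feasibility, as "average work performance scores that do not exceed 0.60 standard deviations (in the direction of poorer performance") of the scores under standard sitting. It gives no limit for improvement. The keyboard standard used as one source of the margin is described there with the same directional wording.
- **One-directional purpose.** Desk Pedaling and Work Performance: "employers will require evidence that pedaling such devices does not compromise work performance". The Abstract's Conclusions frame the aim the same way.
- **Two-directional hypothesis.** Purpose and Hypotheses: the intervention period "will not yield meaningful differences in employees’ work performance".
- **Sizing.** Power and Sample Size: "We assume that an equivalence margin standardized by the standard deviation is 0.60 for the primary outcome", with no direction attached; "We also assume an intracluster correlation of 0.05 and a significance level of 0.05"; "a sample size of 50 (25 dyads) gives 80% power to detect equivalence".

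**The concern.** A criterion bounded only on the side of decline is a non-inferiority rule. TOST succeeds only when both a decline and an improvement beyond the margins are excluded. The two rules agree when performance is unchanged or falls, apart from some difference in power. They part when performance rises: employees who do better while pedaling satisfy the definition and may fail the test.

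This decides the first primary outcome. A reader following the definition could call desk pedaling feasible, while a reader following the test would report that equivalence was not shown. If the choice is left open until results are known, the more favourable rule can be picked. The question the Introduction attributes to employers is whether work suffers, and the upper test has no bearing on it.

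**Working it through.** **Inputs from Power and Sample Size:** margin 0.60 SD, intracluster correlation 0.05, alpha 0.05, n = 50 (25 dyads), power 80%.

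**Assumptions, because the article is silent:** upper bound +0.60 SD (symmetric); true change 0 for the sizing; pre-post correlation r from 0 to 0.7; alpha not Bonferroni-adjusted, as in the sizing paragraph.

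**Step 1: reproduce the stated N.** The design effect for dyads is 1 + (2 − 1) × 0.05 = 1.05. The variance of the change is 2(1 − r) SD², which is 2 SD² at r = 0.

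- TOST: n = 1.05 × 2 × ((1.645 + 1.282)/0.60)² = 49.96, so 50.
- SE of the mean change at n = 50: sqrt(2 × 1.05/50) = 0.2049 SD.
- Lower test alone: Φ(0.60/0.2049 − 1.645) = 0.900.
- TOST: 2 × 0.900 − 1 = 0.800.

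The stated 50 and 80% are therefore a TOST calculation at r = 0. With the t distribution (49 df) the values are 78.6% for TOST and 89.3% for the lower test.

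**Step 2: size for the criterion as written.** One-sided: n = 1.05 × 2 × ((1.645 + 0.842)/0.60)² = 36.06, so 37, or 38 as 19 dyads.

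**Step 3: probability of passing at n = 50.** With SE = sqrt(2(1 − r) × 1.05/50) and true change d in SD units (positive = improvement):

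- one-sided: Φ((0.60 + d)/SE − 1.645)
- TOST: Φ((0.60 − d)/SE − 1.645) − Φ(−(0.60 + d)/SE + 1.645)

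| r | SE | d = 0: TOST / one-sided | d = +0.4: TOST / one-sided | d = +0.6: TOST / one-sided |
|---|---|---|---|---|
| 0 | 0.205 | 80.0% / 90.0% | 25.1% / 99.9% | 5% / about 100% |
| 0.5 | 0.145 | 98.7% / 99.4% | 39.6% / about 100% | 5% / about 100% |
| 0.7 | 0.112 | 99.98% / 99.99% | 55.4% / about 100% | 5% / about 100% |

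Example for r = 0, d = +0.4: TOST = Φ(0.20/0.2049 − 1.645) − Φ(−1.00/0.2049 + 1.645) = 0.2518 − 0.0006 = 0.251; one-sided = Φ(1.00/0.2049 − 1.645) = 0.9994.

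**Step 4: what drives the gap.** At zero change the cost of the second test is 10 points at r = 0 and under 1 point at r = 0.5 or above. Under a real improvement the gap is large at every r, and at +0.60 SD TOST passes 5% of the time whatever the correlation.

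**Step 5: effect of the Bonferroni level.** The figures above use 0.05. If there were 8 comparisons (2 raters × 4 scores, an assumption), alpha would be 0.05/8 = 0.00625. Power at zero change by the t distribution would then be 27.3% for TOST against 63.2% one-sided at r = 0, and 86.9% against 93.4% at r = 0.5. That the sizing uses an unadjusted alpha is a separate matter.

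**The case against.** Much of the text reads as two-sided. The hypothesis speaks of no meaningful differences, the analysis section speaks of equivalence throughout, the sizing margin carries no direction, and N = 50 reproduces as a TOST calculation. On this view the smaller repair is to add the upper margin to the definition. That stands as an acceptable alternative, but it does not remove the conflict, because no sentence reconciles the one-sided definition with the two-bound test.

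Three stronger readings are tempting, and the document does not support them:

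- *That the stated power is wrong.* It is not. The 80% is a TOST figure for a TOST analysis, and the loss relative to a one-sided test nearly vanishes at moderate correlation at the unadjusted level.
- *That the plan risks a false claim of feasibility.* It does not. TOST contains the lower test at the same alpha, so anything that passes TOST also passes the one-sided test. The error runs only towards failing to declare feasibility.
- *That an improvement is expected.* The article does not say so. The hypothesis anticipates no meaningful difference, and Comparison With Prior Work reports only an absence of harm. The +0.4 SD case shows how far the rules can diverge; it is not a forecast.

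The planned mixed-model time effect would reveal an improvement, which softens the harm. It does not say which rule then decides feasibility.

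**Conclusion.** The concern holds as a conflict between the stated success criterion and the stated test for a primary outcome. Its main consequence is an undetermined conclusion when performance improves: at a true +0.4 SD the written criterion is met over 99.9% of the time and TOST about 25% to 55% of the time for r from 0 to 0.7. These figures rest on n = 50, unadjusted alpha 0.05 and an inferred upper bound of +0.60 SD. Lost power at no change is a minor part of the point at that alpha. The text can be reconciled in either direction. The one-sided reading fits the definition, the rationale and the directional keyboard standard better; the hypothesis and the sizing fit the two-sided one.

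**What to change.** Before the outcome data are analysed:

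1. Make the feasibility decision the one-sided test against the 0.60 SD poorer-performance margin that the definition already states. Use the Bonferroni-adjusted one-sided level and the matching lower confidence limit. The lower limit of an ordinary 90% interval would not do, because it corresponds to an unadjusted 0.05.
2. Report the upper TOST bound, with its margin written out, as a separate secondary statement of equivalence.
3. Align the wording of Purpose and Hypotheses, Effects of Desk Pedaling on Work Performance, and Power and Sample Size.

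If the sponsor means true equivalence, keep TOST and write and justify the upper margin in the definition instead.

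The cost is a few sentences and no added participants. The downside of the first route is that the primary claim becomes not meaningfully worse rather than equivalent. Because data collection is under way and the one-sided rule is easier to meet, the change and its date must be recorded as made during data collection and before analysis.
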